### Effect data

Continuous variables will be summarized descriptively providing, where applicable, the number of patients (N), mean, standard deviation (SD), coefficient of variation, median, minimum (min) and maximum (max).

Changes from baseline will be summarized descriptively providing, where applicable, the number of patients (N), mean, standard deviation (SD), median, minimum (min) and maximum (max).

A Student’s T-test will be performed to analyze the changes in the absolute percentage of proliferated T-cells as well as the cell division index over time.

Details on the statistical analysis methods used will be further detailed in the statistical analysis plan.

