| **Statistical methods**  **Statistical analysis methods**  The primary analysis will be done on the treatment period, i.e. once all patients completed the 24 week timepoint. An additional analysis will be performed at week 48.  Safety population  The safety population will comprise of all patients who received at least one dose of treatment.  Full analysis population (FAS)  The full analysis set (FAS) consists of all patients who received at least one dose of treatment and in whom at least one effect assessment is available beyond baseline.  Sample size  Since this is the first study in patients with MS the sample size is based on medical and practical grounds rather than statistical grounds.  Safety parameters  No formal statistics will be employed   - Adverse events (AEs) will be coded and presented using MedDRA. The overall incidence, the incidence of related as well as the incidence of serious adverse events (SAEs) will be summarized per dose and by body system in tables. - Local tolerability will be presented by overall incidence by treatment group per symptom. - Vital signs (supine blood pressure and heart rate) and body temperature: Descriptive statistics (n, mean, standard deviation, median, minimum, and maximum) will be provided for blood pressure, heart rate and body temperature and for changes from baseline. - Hematology, biochemistry and urinalysis parameters: Descriptive statistics (n, mean, standard deviation, median, minimum, and maximum) will be provided on values at baseline and all post-dose assessments. Descriptive statistics will be calculated on the change from baseline values. Out-of-normal-range values will be indicated for each parameter. The change in out-of-normal-range values after administration and at follow up versus baseline will be summarized per group by means of shift-tables. - ECG: Descriptive statistics (frequency, mean, standard deviation, median, minimum, and maximum) on ECG parameters will be provided at baseline and at all post-baseline assessments. Changes from baseline values will be calculated and descriptive statistics will be computed. Shift tables will also be provided to indicate changes in ECG parameters over time.   PK parameters  Descriptive statistics (n, mean, standard deviation, median, minimum, and maximum, plus Geometric mean and CV for C_max_ and AUC and the derived parameters) will be provided for the PK parameters.  Evaluations of dose-proportionality and effects of multiple dosing will be performed.  Effect parameters  Descriptive statistics (n, mean, standard deviation, median, minimum, and maximum) at each visit will be provided for all effect parameters and as well as change from baseline (n, mean, standard deviation, median, minimum, and maximum).  A Student’s T-test will be performed to analyze the changes in the absolute percentage of proliferated T-cells and of the cell division index over time.  Details on the analysis methods to be used for other effect parameters will be specified in the statistical analysis plan. | |

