## Treatment period (week 0-24)

Patients will be hospitalized the evening or the morning before study drug administration and will be discharged from the hospital 24 hours after dosing.

During hospitalization, patients will undergo a series of assessments (see schedule of assessments, section 6.5). The last available values measured prior to first study drug administration will be considered baseline measurements against which measurements during the treatment period will be compared.

Patients are to refrain from exercise other than the normal daily activities for 24 hours after injection of study medication.

On dosing days study drug administration will take place in the morning upon completion of all necessary pre-dose assessments. The following assessments will be performed: vital signs, ECG, safety biochemistry and haematology, urinalysis and biomarkers. In addition, blood sampling for PK will be performed on the first dosing day. Twenty-four hours after the study drug administration, AEs will be assessed and the patient will be discharged if in good general health. Hereafter the patients will leave the unit.

Patients will return to the hospital for ambulatory visits or hospitalization for the treatment administration visits according to the schedule of assessments, section 6.5.

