## Effect variables

### T-cell response

Two 10 mL blood samples will be taken for assessment of T-cell responses (CD4+ and CD45RO+) to DC-TAB and to the unrelated control antigen tetanus toxoid. Peripheral blood samples are to be collected in heparin tubes to prevent blood clotting, and kept at room temperature, also during transport, until they are processed. Samples should be shipped to the regional laboratory by courier, ensuring delivery preferably within 4 h after sampling, but no later than 6 h after sampling.

T-cell responsiveness assays will be initiated on the day of sample collection. Peripheral blood mononuclear cells (PBMC) will be isolated from blood samples within 8 h after sampling, and immediately subjected to an assay for antigen-specific proliferation. The cell culture assay to determine antigen-specific responses of T cells to either DC-TAB itself, or to tetanus toxoid as a control antigen Peripheral mononuclear cells will be isolated from blood samples, labeled with the fluorescent dye carboxyfluorescein succinimidyl ester (CFSE), and placed in culture with antigen at doses known to stimulate maximum proliferative responses. After 9 days, cells will be harvested, additionally stained with fluorescently labeled antibodies to either CD4 (a marker for helper T cells) or CD45RO (a marker for memory T cells of both the CD4 and CD8 lineage), and subjected to flowcytometry. During flowcytometry, cells will be scored for levels of the original CFSE label, and levels of the additional CD4 or CD45RO marker. Since the CFSE label in a mother cell is equally distributed over its resulting daughter cells, proliferated cells are typified by reduced levels of CFSE, especially after several rounds of cell division. Flowcytometry thus allows quantitation of the fraction of either CD4 or CD45RO cells which have proliferated in culture in response to antigen. All data points will be collected at least in triplicate, with each data point being collected using the combined cells of six individual culture wells.

T-cell responses will be assessed by the Central Reference Laboratory for Immunology, at the National Center for Infectious and Parasitic diseases, Sofia, Bulgaria.

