### Effect parameters and endpoints

Effect parameters

- - Proliferative CD45RO+ (memory) and CD4+ (helper) T-cell response to DC-TAB
  - New or enlarging gadolinium-enhancing lesions on T1-weighted MRI
  - Clinical relapse
  - EDSS
  - MSIS-29
  - Levels of serum antibodies against CRYAB/DC-TAB

Exploratory effect endpoints

- Change in T-cell responses (CD4+ and CD45RO+) to DC-TAB throughout the study
- Cumulative number of new or enlarging gadolinium-enhancing MRI lesions between week 4 and 24, and week 4 and 48 first dose, relative to baseline
- The number of clinical relapses between week 0 and week 24, and week 0 and week 48
- Change in EDSS score between week 0 and week 24, and week 0 and week 48
- Change in MSIS-29 score between week 0 and week 24, and week 0 and week 48
- Change in levels of CRYAB/DC-TAB-reactive serum antibodies
- Change in neutralizing activity of CRYAB-reactive serum antibodies

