### Pharmacokinetic data

Plasma concentrations will be listed and summarized by nominal time point, and treatment (number of patients (N), mean, standard deviation, minimum, median maximum, coefficient of variation). Individual and mean plasma concentration vs. time profile plots will be produced for each dose level.

All pharmacokinetic calculations will be done using WinNonlin (version 5.2 or higher). Pharmacokinetic parameters will be listed and summarized by treatment.

Statistical analyses of pharmacokinetic data will include enrolled patients who receive study treatment and complete the study. The AUC_last_, AUC_inf_ and C_max_ parameters will be analyzed both prior to and after natural log transformation, as applicable. The pharmacokinetic parameter estimates will be evaluated by Analysis of Variance.

Details will be described in the statistical analysis plan.

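### The t-test named for the T-cell data states no contrast with placebo, and the tetanus control is in no endpoint or analysis, so antigen-specific tolerance is not tested as written

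*Protocol*

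**What the plan says.** Section 10.3.4 (Effect data) names Student's test: "T-test will be performed to analyze the changes in the absolute percentage of proliferated T-cells as well as the cell division index over time". The synopsis, under statistical methods, repeats it: "T-test will be performed to analyze the changes in the absolute percentage of proliferated T-cells and of the cell division index over time". Neither place says whether the test is paired within an arm or compares arms. Neither mentions placebo, a time point or a significance level.

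What is left open differs between the two places. The synopsis adds: "Details on the analysis methods to be used for other effect parameters will be specified in the statistical analysis plan". The deferral there is for the other effect parameters, after the t-test has been fixed for the T-cell data. Section 10.3.4 ends: "Details on the statistical analysis methods used will be further detailed in the statistical analysis plan".

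The T-cell endpoint in section 10.1.2 is "Change in T-cell responses (CD4+ and CD45RO+) to DC-TAB throughout the study". Section 7.4.1 provides for "assessment of T-cell responses (CD4+ and CD45RO+) to DC-TAB and to the unrelated control antigen tetanus toxoid". Tetanus does not appear again in the effect parameters, the endpoints or the analysis text, in the synopsis or in section 10. Secondary objective 1 (section 3.2) is nevertheless about antigen-specific tolerance, and section 4.3 justifies the placebo arm as a means of limiting bias and correcting for placebo effects.

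Section 6.2 defines baseline: "The last available values measured prior to first study drug administration will be considered baseline measurements".

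**The concern.** There are two gaps.

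First, the only contrast that the wording gives is time. A before-after test in a treated arm cannot separate the drug from anything else that moves the assay in every arm, such as reagent lots, cell handling, season or background MS treatment. The randomized control that could make the separation is not mentioned. Setting a significant result in an active arm beside a non-significant one in the placebo arm does not replace a direct comparison.

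Second, specificity is a claim about two antigens. A fall in the response to DC-TAB alone could be tolerance or general suppression. The protocol allows systemic corticosteroids for relapses, and interferon-beta or glatiramer where judged necessary (sections 4.4.3 and 7.4.4). The tetanus response is the measurement that would tell the two apart, and it has no place in the analysis.

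The T-cell result is put to use. Section 4.1 lets its duration bear on the interval between treatments and has the safety review verify adequate tolerization. Section 5.2 seeks information on the optimal dose. Section 10.5 expects information on effect, alongside safety, to support a larger Phase 2b study.

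**Working it through.** **The plan's own figure.** Four arms of 8 give 4 × 8 = 32, which agrees with the synopsis. Section 10.5 gives no power, effect size, SD or significance level, so there is nothing further to reproduce.

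**Assumptions for the illustration (none is in the protocol).** Two-sided 5% level, normal data, no dropout, single-visit SD of 1, and correlation r between any two visits of the same patient of 0.3, 0.5 or 0.7.

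**1. Within-arm test under a common shift.** The SD of a change is √(2(1−r)). With a shift of 0.5 in every arm and no drug effect, the paired t-test in one arm has 7 df and noncentrality 0.5 × √8 / √(2(1−r)).

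| r | SD of change | noncentrality | falsely positive |
|---|---|---|---|
| 0.3 | 1.18 | 1.20 | 18% |
| 0.5 | 1.00 | 1.41 | 23% |
| 0.7 | 0.77 | 1.83 | 35% |

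With the shift expressed in SDs of the change, 0.25, 0.5, 0.75 and 1.0 give 9%, 23%, 45% and 68%. A two-sample test of change against placebo stays at 5% throughout, because the shift cancels.

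**2. Price of the placebo contrast.** For 80% power, one arm tested against its own baseline needs a change of 1.16 SD of change. Eight against eight needs a difference of 1.51.

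**3. What baseline adjustment returns.** In units of the single-visit variance, a change score has variance 2(1−r) = 1.40, 1.00, 0.60 at r = 0.3, 0.5, 0.7. Covariate adjustment has 1−r² = 0.91, 0.75, 0.51. For a true difference of 1 single-visit SD at week 24:

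- Two-sample t-test on change (14 df, noncentrality 2/√(2(1−r)) = 1.69, 2.00, 2.58): power 35%, 46%, 67%.
- One four-arm model adjusted for the day-0 value (27 df, 20,000 simulated trials per correlation): power 51%, 59%, 76%. With the mean of the screening and day-0 values as covariate, the range is 53-83%.

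**4. Specificity.** If treatment lowers the DC-TAB and tetanus responses equally by d, the contrast of the DC-TAB response with placebo has expectation d, exactly as under true tolerance. For d = 1 SD of change it is significant in 46% of trials, although nothing specific has happened. The difference between the two antigens' treatment effects has expectation d − d = 0. If both responses have the same variance and correlate ρ within a patient, the variance of that difference is 2(1−ρ) times that of one contrast, so it is less precise when ρ is below 0.5.

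**5. Is a dose trend a better lead contrast?** Centred on their mean of 9.375, doses 0, 7.5, 12.5 and 17.5 mg become −9.375, −1.875, 3.125 and 8.125, with sum of squares 167.19. Suppose only 12.5 mg works, by 1 SD. The trend has noncentrality (3.125/√167.19) × √8/σ = 0.68/σ, against 2/σ for 12.5 mg versus placebo, or about one third. For the week 4-24 average (six visits) adjusted for the day-0 value, σ = √(r + (1−r)/6 − r²) = 0.57, 0.58, 0.51. Simulated power is 21-25% for the trend as a contrast in the four-arm model, and about 10% when a straight line replaces the arm terms. The pairwise contrast has 90-96%.

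**The case against.** The strongest reply is that the protocol leaves the comparator open and does not exclude placebo. A t-test on changes can be a two-sample test against placebo, section 4.3 gives the placebo arm a corrective role, and section 10.3.4 promises further detail in the analysis plan. This stands as far as it goes. A reader might infer that the sponsor will ignore the placebo arm, or that the trial cannot show specificity. The text supports neither. It supports only that the plan, followed as written, does not require the placebo contrast and does not test specificity.

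Other stronger readings also fail:

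- This is not the only inferential method in the protocol. Section 10.3.3 says: "The pharmacokinetic parameter estimates will be evaluated by Analysis of Variance". It is the only test named for the effect data.
- Baseline is not ignored, since a change score uses it. Only adjustment for it as a covariate is absent.
- A count of all possible tests by subset, readout, visit and dose would hold endpoints labelled exploratory to a confirmatory standard.
- No rule makes this readout alone decide the dose or the Phase 2b start. Section 10.5 cites safety and effect together.
- Relapse steroids are not confined to the active arms, so a placebo contrast would largely deal with them. They do not by themselves make the case for tetanus. The antigen-specific objective does.

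It is also fair that no passage reports assay drift, so the 0.5 SD is only an illustration. What the reply does not reach is the tetanus gap. It lies in the protocol's own endpoint list, and choosing between a paired and a two-sample t-test does not close it.

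**Conclusion.** The point holds in this form: the one test named for the effect data states no contrast with placebo, and the control antigen measured for specificity enters no endpoint or analysis. Secondary objective 1 is therefore not tested as written.

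The tetanus gap is the firmer half and needs no assumption. The size of the first gap depends on the reading. If the test is within-arm and all arms shift by an assumed 0.5 single-visit SD, each test is falsely positive in 18-35% of trials. If it is a two-sample test against placebo, that error disappears, and what remains is lower power than a baseline-adjusted contrast would have (35-67% against 51-76% for an assumed 1 SD effect at week 24).

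This should be fixed, but it does not undermine the trial. The primary objective is safety, the endpoints are exploratory, and the data needed are already being collected.

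**What to change.** In section 10.3.4 and the synopsis, replace the Student's t-test with a baseline-adjusted comparison of each dose with placebo, with all four arms in one model. Either analysis of covariance on the week 4-24 average or a repeated-measures model over weeks 4-24 would serve.

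In section 10.1.2 and the synopsis list, add the response to tetanus toxoid as a specificity endpoint, analysed in the same model. Judge specificity by the difference between the DC-TAB and tetanus treatment effects, not by a non-significant tetanus result. State the scale on which the two effects are compared.

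A log transform, averaging the two pre-dose values, handling of multiplicity and a linear dose trend are optional choices for the analysis plan. The trend should not be the lead contrast, because it loses most of its power if the response is not monotone in dose.

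The cost is wording and slightly more analysis work, with no new samples or visits. A contrast with placebo is less precise than a within-arm change, and the between-antigen difference may be less precise still. Section 4.1 says T-cell results are known two weeks after sampling, so the change should be fixed before anyone involved in the analysis sees them by treatment.

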### Demographic and background variables

Baseline demographic and background variables will be summarized for all patients. For categorical variables, frequencies and percentages will be provided. For continuous variables, descriptive statistics including the sample size, mean, median, standard deviation and range, will be presented.

### Patient accountability

All patients enrolled will be included in a summary of patient accountability. The frequency and percentage of patients enrolled in the study, randomized, discontinued before completing the study, and completing the study will be summarized.

### Study medication compliance

A summary of study medication usage and compliance will be provided for all patients by treatment group.

## Blinded Safety Review Analysis

Three blinded safety review analyses will be performed, after 12 patients have completed the visits at week 4 and 12 and after 24 patients have completed the visit at12 weeks.

An independent DSMB will be constituted to evaluate the blinded safety data. Data of patients with serious adverse events may be unblinded at the request of the DSMB. If the safety evaluation by the DSMB reveals any investigational product-related serious adverse events, the corresponding dose regimen may be discontinued.

## Sample size justification

The number of patients to be included is based on medical rather than statistical grounds. It is considered that the foreseen number of patients per dose group will provide sufficient safety information and information on the effect of DC-TAB to start a larger Phase 2b study in this patient population.

## Study report

At the conclusion of the study, after the data are analyzed, the sponsor will prepare an integrated study report in accordance with ICH-E3. A draft copy of the report will be available for review by the PI. The report will be signed by the PI and appropriate persons from the sponsor.

# Adverse events

## Adverse event definition

An adverse event is any untoward medical occurrence in a patient or clinical investigation patient administered a pharmaceutical product and which does not necessarily have a causal relationship with this treatment. An adverse event (AE) can therefore be any unfavourable and unintended sign (including a laboratory finding), symptom or disease temporarily associated with the use of a medicinal product, whether or not related to the medicinal product.

Adverse events may include, but are not limited to:

- Subjective or objective symptoms spontaneously offered by the patient, parent/legal representative or observed by the investigator or medical staff.
- Laboratory abnormalities of clinical significance.

Disease signs, symptoms and/or laboratory abnormalities already existing prior to the use of the product are not considered adverse events after treatment unless they reoccur after the patient has recovered from the pre-existing condition or in the opinion of the investigator they represent a clinically significant exacerbation in intensity or frequency.

## Reporting adverse events

At each evaluation, the investigator will determine whether any adverse events have occurred. If any adverse events have occurred, they will be recorded on the adverse event report pages of the CRF. If known, the diagnosis should be recorded, in preference to the listing of individual signs and symptoms.

Any adverse event experienced by the patient from the time of signing the informed consent until the end of the study will be recorded in the CRF.

The investigator will be asked to assess the severity of the adverse drug/ biologic event using the following categories: mild, moderate and severe. This assessment is subjective and the investigator should use medical judgment to compare the reported adverse event to similar type events observed in clinical practice. Below are listed guidelines for severity assessment:

Mild: Symptom(s) barely noticeable to the patient or does not make the patient uncomfortable. The adverse event does not influence performance or functioning. Prescription drugs are not ordinarily needed for relief of symptom(s).

Moderate: Symptom(s) of a sufficient severity to make the patient uncomfortable. Performance of daily activities is influenced. Treatment of symptom(s) may be needed.

Severe: Symptom(s) of a sufficient severity to cause the patient severe discomfort. Severity may cause cessation of treatment with the study drug. Treatment for symptom(s) may be given.

The investigator will make a judgment regarding whether or not, in his/her opinion, the adverse event was related to study drug. The investigator will also evaluate any changes in laboratory values, make a determination as to whether the change is clinically important, and whether or not the changes were related to study drug. However, even if the investigator feels there is no relationship to the study drug, the adverse event or laboratory abnormality must be recorded in the CRF.

If the relationship between the study drug and the adverse event is defined as “not related”, then the adverse event must definitely be caused by the patient’s clinical state, or the study procedure/conditions.

A “remote/unlikely” relationship is defined as when the temporal association between the adverse event and the drug is such that the drug is not likely to have any reasonable association with the adverse event.

A “possible” relationship is defined as when an adverse event could have been produced by the patient’s clinical state or the therapy.

A “probable” relationship is defined as when the adverse event follows a reasonable temporal sequence from the time of drug administration, abates upon discontinuation of the drug and cannot be reasonably explained by the known characteristics of the patient’s clinical state.

A “definite” relationship is defined as when the adverse event follows a reasonable temporal sequence from the time of drug administration, abates upon discontinuation of the drug and reappears when the drug is introduced.

